1  
2  
3  
4  
5  
6  
7  
8  
9  
10  
11  
12  
13  
14  
15  
16  
17  
18  
19  
20  
21  
22  
23  
24

### Statement of compliance

This study will be conducted in compliance with all stipulations of this protocol, the conditions of the ethics committee approval, and the NHMRC National Statement on Ethical Conduct in Human Research (2023).

### Trial registration

This trial was registered with the Australian New Zealand Clinical Trials Registry (ANZCTR) September 25 2024. Registration number: **ACTRN12624001176550**

### Document history

| Version Number and Date  | Summary of changes                                                               |
|--------------------------|----------------------------------------------------------------------------------|
| Version 1:
01/10/2024 | Original protocol submitted with ethics application                              |
| Version 2:
17/11/2025 | Updated to include full trial registration details and revised funding statement |

## 1. STUDY SYNOPSIS

### 1.1. EXECUTIVE SUMMARY

This study is part of the TRAVel VACCine Decision Aids for Decision-making (TRAVAID) Project, which is establishing a platform for the development of a suite of evidence-based travel vaccine decision aids for travel medicine. This protocol details a randomised controlled trial (RCT), that will measure the impact of a co-designed Japanese Encephalitis VACCine Decision Aid (JEVaDA) compared with standard practice (a fact sheet) on vaccine decision-making for Japanese encephalitis (JE) in a cohort of Australian travellers.

### 1.2. KEY DETAILS

|                               |                                                                                                                                                                                                                                                                                                                         |
|-------------------------------|-------------------------------------------------------------------------------------------------------------------------------------------------------------------------------------------------------------------------------------------------------------------------------------------------------------------------|
| TITLE                  | Evaluation of a Vaccine Decision Aid for Japanese Encephalitis (JE)                                                                                                                                                                                                                                                     |
| SHORT TITLE            | JE Vaccine Decision Aid Trial                                                                                                                                                                                                                                                                                           |
| OBJECTIVES             | The aim of this study is to assess the effectiveness of a co-designed Japanese Encephalitis Vaccine Decision Aid (JEVaDA) compared to standard practice on JE vaccine decision-making amongst Australian travellers.                                                                                                    |
| DESIGN                 | Individually randomised, single-blinded, controlled trial                                                                                                                                                                                                                                                               |
| OUTCOMES               | Our primary outcome is to evaluate whether the JE decision aid reduces decisional conflict (as measured by the decisional conflict scale) compared to standard practice.

Secondary outcomes include evaluating the impact of the decision aid on JE knowledge, intention to vaccinate and actual vaccine uptake. |
| STUDY DURATION         | 1 year                                                                                                                                                                                                                                                                                                                  |
| NUMBER OF PARTICIPANTS | 500                                                                                                                                                                                                                                                                                                                     |
| STUDY LOCATION         | Melbourne, Australia                                                                                                                                                                                                                                                                                                    |
| Funding                | National Health and Medical Research Council (2017229-RSP)                                                                                                                                                                                                                                                              |

## 84 1.5. GLOSSARY OF ABBREVIATIONS AND TERMS

| Abbreviation/term | Description                                     |
|-------------------|-------------------------------------------------|
| AMR               | Antimicrobial resistance                        |
| COVID-19          | Coronavirus Disease 2019                        |
| DCS               | Decisional Conflict Scale                       |
| IPDAS             | International Patient Decision Aids Standards   |
| ISTM              | The International Society of Travel Medicine    |
| JE                | Japanese encephalitis                           |
| MMR               | Measles, mumps & rubella                        |
| RCT               | Randomised controlled trial                     |
| REDCap            | Research Electronic Data Capture                |
| SPHPM             | School of Public Health and Preventive Medicine |
| VCI               | Vaccine Confidence Index                        |
| VPD               | Vaccine preventable diseases                    |

85

## 86 2. INTRODUCTION/BACKGROUND INFORMATION

87 Travellers play a key role in the global spread of infections, and as Australia has now fully re-opened  
88 its borders following COVID-19 disruptions, travel-related infection acquisition and importation is  
89 increasing. Pre-travel vaccination is a key preventive intervention for vaccine-preventable diseases  
90 (VPDs), but comes at a cost; factors contributing to poor uptake include low risk perceptions and  
91 willingness (and capacity) to pay. While the COVID-19 pandemic has drawn attention to VPDs, it  
92 has also led to increasingly polarised vaccine attitudes, highlighting the need for health  
93 communication strategies that can address vaccine misinformation and support vaccine-related  
94 decision-making. Vaccine decision aids are evidence-based tools designed to provide patients with  
95 high-quality information on vaccine risks and benefits, help them clarify and communicate personal  
96 values, and guide them through the decision-making processes; they can also be used to support

shared-decision making with healthcare providers. Decision aids for influenza and MMR vaccines have been shown to reduce decisional conflict and increase vaccine uptake, but to date no studies have reported on development or evaluation of decision aids for travel-related VPDs.

Among travel-related VPDs, JE stands out as a disease for which improved vaccine communication resources are needed. The uptake of JE vaccine amongst travellers to endemic areas is particularly poor, noting that travel to JE-endemic regions (comprising many Asia-Pacific countries) is common among Australians. The unpredictability of JE epidemiology, its propensity to cause severe disease and death (including in short-term travellers) and expansion to new geographic areas (including 2022 detection in four Australian states) make a compelling case to consider more widespread vaccination, including for travellers to endemic areas. Currently available vaccines are safe and efficacious but vaccine decision-making is complicated by the availability of two vaccine options with different schedules, costs and duration of protection. Typhoid is another important travel-related VPD for which vaccine uptake in travellers to endemic regions is low despite considerable risk. With rates of antimicrobial resistance (AMR) amongst *S. Typhi* strains increasing, particularly in Asia which is a common travel destination for Australians, prevention through vaccination is increasingly important. As with JE, multiple vaccine options, including live vaccines, are available for typhoid, increasing decision-making complexity. Evidence-based decision aids for travel-related VPDs could potentially increase travellers' understanding of disease risks, empower them to make informed decisions, and enhance pre-travel vaccine uptake to reduce disease importation.

### 3. STUDY OBJECTIVES

#### 3.1. HYPOTHESIS

We hypothesise that a co-designed Japanese Encephalitis Vaccine Decision Aid (JEVaDA) will reduce decisional conflict regarding JE vaccination compared to usual practice. This reduction in decisional conflict is expected to help users make higher-quality decisions that better align with their values.

We also hypothesise that by facilitating more informed and value-aligned decisions, JEVaDA will increase both the intention to vaccinate (planning to receive the vaccine before travel) and actual vaccine uptake. Additionally, we expect that JEVaDA will enhance knowledge related to JE.

#### 3.2. STUDY OBJECTIVES

Guided by the Ottawa Decision Support Framework (ODSF), the main goal of this research is to assess the impact of a decision aid (JEVaDA) on Australian travellers' decision-making related to Japanese encephalitis (JE) vaccines. JEVaDA, co-designed with input from consumers and healthcare providers, is an online tool that aims to facilitate informed decision-making by helping travellers understand and visualise the risks, benefits and trade-offs of different choices, relate personal values to available options, and make choices aligned with their values.

Our primary outcome is to evaluate whether the JE decision aid reduces decisional conflict (as measured by the decisional conflict scale) compared to standard practice.

136 Secondary outcomes include evaluating the impact of the decision aid on JE knowledge, intention to  
137 vaccinate and self-reported vaccine uptake.

## 138 **4. STUDY DESIGN**

139 This study will use an individually randomised, single-blinded, controlled trial design. Prospective  
140 Australian overseas travellers will be recruited through a consumer panel provider to participate in  
141 the trial.

142 Participation in the trial will involve three steps, plus an optional follow up. Participants will first  
143 complete an initial (pre-intervention) survey (Step 1). They will then be randomly assigned to either  
144 the intervention or control group and receive a link to the corresponding materials based on their  
145 group assignment. Participants will be instructed to keep the REDCap survey open in a separate  
146 browser tab while reviewing the assigned materials (Step 2). After reviewing the materials, they will  
147 return to the REDCap browser to complete a post-intervention survey (Step 3). Participants who  
148 complete Step 1 but do not commence Step 3 will be sent up to two invitational reminders via email  
149 between 48-72hrs after completion of Step 1. Additionally, participants will be asked to consent to  
150 be contacted 3-6 months after the initial survey to complete an optional follow-up survey. This  
151 follow-up will investigate whether they undertook travel and received JE vaccine. Participants may  
152 opt out of this follow-up contact if they choose.

### 153 **4.1. INTERVENTION ARM**

154 Participants randomised to the intervention arm will receive a link to the online Japanese  
155 encephalitis vaccine decision aid (JEVaDA) tool. This tool has been developed in accordance with  
156 International Patient Decision Aids Standards (IPDAS – Appendix 1) and designed through a  
157 comprehensive co-design and user-testing framework.

158 The JEVaDA tool features a self-guided, step-by-step approach divided into three main sections, with  
159 additional pages such as an FAQ. It provides detailed information on Japanese encephalitis, including  
160 its geographic distribution, modes of transmission, clinical features, severity and risk. It also covers  
161 preventive measures, including mosquito bite avoidance strategies and a comparison of available  
162 vaccines in Australia. Participants are encouraged to reflect on their personal circumstances and how  
163 their beliefs and values align with their intended decision, and are prompted to consult with their  
164 healthcare provider to discuss their options.

165 The tool includes visual aids and interactive elements designed to support decision-making, such as a  
166 side-by-side risk-benefit analysis graphic and a values clarification exercise. JEVaDA is intended as an  
167 educational resource and emphasises the importance of consulting with a trusted healthcare  
168 provider before making a vaccination decision.

169 A downloadable short-form PDF version of the decision aid is available on the website. This PDF  
170 version contains a condensed version of the online content and lacks the interactive features of the  
171 online tool.

The time participants spend using the decision aid will vary based on their engagement with the content. Based on pilot testing, we anticipate that most users will spend approximately 15 minutes or less with the tool.

## **4.2. CONTROL ARM**

Participants randomised to the control arm will receive a link to an online health information page about JE managed by Healthdirect Australia. As the national virtual public health information service, Healthdirect Australia collaborates with federal, state and territory governments to provide a range of evidence-based health resources. Their platform features over 2,000 evidence-based and clinically safe pages of information.

The Healthdirect Australia JE webpage provides information on JE, including its geographic distribution, modes of transmission, symptoms and severity. It also covers preventive options, including mosquito bite avoidance and vaccines available in Australia.

The information is organised into a single, continuous webpage, with key details broken down into sub-section. The page includes tools for symptom checking and finding local health services, as well as accessibility features such as text enlargement, page-masking and text-to-speech capabilities.

A print to PDF function is available at the top of the page, and links to additional resources and support are also included. Users are informed that reading the page in full takes approximately 11-minutes.

## **4.3. GOVERNANCE**

This project will be overseen by a Steering Group including investigators listed in Section 1.4 of this protocol. Meetings will take place at regular monthly intervals and will be held via Zoom. Additional meetings will be arranged as necessary.

In addition, we will host at least one consumer representative position as a member of the Steering Group. The role and expectations of the consumer representative (including commitment to privacy and confidentiality) are outlined in Appendices 2 and 3.

# **5. STUDY METHODOLOGY**

## **5.1. RECRUITMENT**

We will recruit participants through the Online Research Unit (ORU), Australia's leading data collection agency (<https://www.theoru.com/>). The ORU specialises in delivering high-quality, purpose-built consumer panels and manages a nationally representative panel of over 350,000 active Australian members, profiled across diverse demographics. The ORU distinguishes itself by conducting the majority of its recruitment through offline methods, such as telephone, mail and print, in addition to its online recruitment efforts. This approach includes a double opt-in process and mailing incentives to respondents' residential addresses, which serves as a robust validation tool

to confirm participants' residency in Australia and ensure authenticity. All surveys are de-identified, and no personal identifying information will be shared with the research team.

Using a random stratified sampling approach, the ORU will distribute a survey link to a targeted subset of their panel members who meet the initial eligibility criteria: being 18 years or older and currently residing in Australia. The survey link will be sent via their online platform. After accessing the link, panel members will be screened for an additional criterion: a stated intention to travel to an Asian country where JE is a risk within the next 6 months. A list of at-risk countries and a map will be provided for reference. Respondents will be sampled to ensure national representativeness based on age, sex and geographic location. The ORU will continue to invite additional respondents as necessary to achieve the required demographic balance, adjusting for any under-represented groups based on completion rates.

### 5.1.1. SELECTION CRITERIA

In order to be considered eligible to participate in this study, participants must be:

- Age 18 years or older
- Currently living in Australia
- Able to read and understand English
- Planning travel to a JE-endemic region within the next 6-months

## 5.2. RANDOMISATION

Individually stratified randomisation will be used to allocate participants to either the intervention or control group. This process will ensure that groups are balanced according to baseline demographic characteristics collected from the pre-intervention survey, including age group, gender and geographic location (state or territory of residence). We will utilise the automated randomisation module in REDCap, with access requested from the Monash Helix team. To maintain blinding, a statistician independent of the central research team will build and upload the randomisation tables to REDCap. Participants will be randomly assigned to their respective groups based on their survey responses. Upon completion of the pre-intervention survey, participants will be directed to the materials corresponding to their assigned group based on the randomisation outcome.

### 5.3. DETAILS OF PARTICIPANT INVOLVEMENT

Participation in the trial involves three steps, all completed in a single web-based session (Figure 1):

- Step 1: Pre-intervention survey (approximately 7-10 minutes): all participants will complete the same survey
- Step 2: Review of assigned information (approximately 15 minutes): participants will be randomised to review either the JEVaDA tool (intervention) or the Healthdirect JE page (control)

Figure 1: Flowchart of Participant Involvement

[figure not shown]

- Step 3: Post-intervention survey (approximately 5 minutes): all participants will complete the same survey

Participants who complete both the pre- and post-intervention surveys will be considered to have provided complete responses. The total estimated time commitment is up to 30 minutes.

Participants will also be asked to consent to a follow-up contact 3-6 months after the initial survey for an optional follow-up survey. This follow-up will assess whether they travelled and received the JE vaccine. Participants can choose to opt out of this follow-up contact. Those who do not opt out will be asked to complete a brief (5 minute) follow-up survey 3-6-months post-intervention.

Since this trial is conducted online, participants must have access to an internet connection in order to participate.

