## **5.8. DATA COLLECTION**

All data will be collected via online surveys using REDCap (Research Electronic Data Capture), a secure, web-based application designed to support data capture for research studies. The surveys (Appendix 10) will gather information on participants' demographics, travel history, general health, health literacy, and JE vaccination history. Additionally, we will assess decisional conflict, knowledge, intention to vaccinate, and vaccine confidence as previously outlined. Questions from the WHO's Behavioural and Social Drivers (BeSD) survey will also be included to evaluate behavioural and social factors influencing vaccination decisions. Furthermore, self-reported JE vaccine uptake data will be collected through an opt-out follow-up survey administered 6 months post-intervention.

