### 665 Travel experiences

666

667 **You mentioned you'll be visiting a JE-risk area in the next 6 months. We'd now like to ask you**  
668 **some questions about your planned trip.**

669

670 How many countries do you plan to visit during this trip?

- 671 ☐ 1  
672 ☐ 2  
673 ☐ 3 or more

674

675 **If one:** Which country are you planning to visit during your upcoming trip? (Drop-down list – i.e.  
676 must select one only)

677 **If two:** What is the first country you are planning to visit during your upcoming trip? (Drop-down list)

678 **If two:** What is the second country you are planning to visit during your upcoming trip? (Drop-down  
679 list)

680 **If three:** What is the third country you are planning to visit during your upcoming trip? (Drop-down  
681 list)

682

683 When are you planning to start your trip?

- 684 ☐ November, 2024  
685 ☐ December, 2024  
686 ☐ January, 2025  
687 ☐ February, 2025  
688 ☐ March, 2025  
689 ☐ April, 2025  
690 ☐ May, 2025

691

692 How long do you plan to travel for?

- 693 ☐ less than one month  
694 ☐ 1 month or more

695

696 Where do you plan to spend the most time during your trip?

- 697 ☐ More than half my time in cities  
698 ☐ More than half my time in rural areas (areas with a lot of farms or forests)  
699 ☐ About the same amount of time in both cities and rural areas  
700 ☐ Not sure

701

702 Are you planning to consult a healthcare provider for travel health advice for this trip?

- 703 ☐ Yes, I'm planning to  
704 ☐ Yes, I've already done so  
705 ☐ No, I'm not planning to  
706 ☐ Not sure

707

708 If yes, where do you plan to get travel health advice from? (select all that apply)

- 709 ☐ General practitioner / primary care  
710 ☐ Travel medicine clinic  
711 ☐ Pharmacist  
712 ☐ Internet  
713 ☐ Friend or relative  
714 ☐ Travel agent  
715 ☐ Other, please specify

716

717 **This set of questions asks about your past travel experiences.**

718

719 Have you ever travelled overseas (outside of Australia)?

- 720 ☐ Yes  
721 ☐ No → skip to "How many overseas trips..."

722

723 In what year was your last overseas trip? \_\_\_\_\_ (Dropdown box: 2014 or earlier to 2024)

724

725 How many overseas trips have you taken in your lifetime? (select one only)

- 726 ☐ 1 or 2  
727 ☐ 3 or 4  
728 ☐ Between 5 and 10  
729 ☐ More than 10  
730 ☐ None → skip next 4 questions

731

732 Which of the following regions have you visited in your lifetime? (select all that apply):

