| I am clear about which is more important to me (the benefits or the risks and side effects) |                |       |                            |          |                   |
| I have enough support from others to make a choice                                          |                |       |                            |          |                   |
| I am choosing without pressure from others                                                  |                |       |                            |          |                   |
| I have enough advice to make a choice                                                       |                |       |                            |          |                   |

|                                           |  |  |  |  |  |
|-------------------------------------------|--|--|--|--|--|
| I am clear about the best choice for me   |  |  |  |  |  |
| I feel sure about what to choose          |  |  |  |  |  |
| This decision is easy for me to make      |  |  |  |  |  |
| I feel I have made an informed choice     |  |  |  |  |  |
| My decision shows what is important to me |  |  |  |  |  |
| I expect to stick with my decision        |  |  |  |  |  |
| I am satisfied with my decision           |  |  |  |  |  |

966

967

1009 [Questionnaire](#)

---

1010

1011 In late 2024, you were planning a trip to a JE endemic area in [pipe previous answer]. Did you take  
1012 your trip as planned?

1013 - Yes – skip to ‘please select the country you spent the most time in from the drop-down list’

1014 - No

1015 How did your plans change?

1016 - Cancelled the trip

1017 - Chose a different destination

1018 - Delayed the trip

1019 - Other (please specify)

1020 Please provide any further details about why your travel plans changed (optional). *Free text box.* –

1021 **end survey**

1022 Please review this list of countries before answering the next question:

1023 ☐ Bangladesh

1024 ☐ Bhutan

1025 ☐ Brunei Darussalem

1026 ☐ Burma (Myanmar)

1027 ☐ Cambodia

1028 ☐ China

1029 ☐ India

1030 ☐ Indonesia

1031 ☐ Japan

1032 ☐ Lao People’s Democratic Republic

1033 ☐ Malaysia

1034 ☐ Nepal

1035 ☐ North Korea

1036 ☐ Pakistan

1037 ☐ Papua New Guinea

1038 ☐ Philippines

1039 ☐ Russia

1040 ☐ Singapore

1041 ☐ South Korea

1042 ☐ Sri Lanka

1043 ☐ Taiwan

1044 ☐ Thailand

1045 ☐ Timor-Leste

1046 ☐ Vietnam

1047

1048 Since November 2024, have you travelled to any of the countries listed above?

1049 ☐ Yes

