### 1.2 General principles

Analysis and reporting of results will follow the CONSORT guidelines.[1] Baseline characteristics will be tabulated by intervention group (JEVaDA) and comparator group (HealthDirect JE fact sheet) using appropriate summary statistics. Data will be derived from those patients who meet inclusion criteria (currently living in Australia, aged 18 years or older, able to read and understand English and intend to travel to a country outside of Australia where JE is a risk within the next 6 months) and enrol in the study.

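### The uptake follow-up may go out before participants have travelled, and its printed routing bypasses the uptake question for them, for changed trips and for those who saw no healthcare provider

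*Combined protocol and SAP*

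**What the plan says.** **Eligibility.** Protocol Section 5.1.1 requires "Planning travel to a JE-endemic region within the next 6-months". SAP Section 1.2 has the same horizon: "intend to travel to a country outside of Australia where JE is a risk within the next 6 months". The pre-intervention survey (Appendix 4, Travel experiences) asks "When are you planning to start your trip" and offers seven months, November 2024 to May 2025.

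**Follow-up timing.** Protocol Sections 4 and 5.3 give a window of 3 to 6 months. Section 5.3 states it twice: "Participants will also be asked to consent to a follow-up contact 3-6 months after the initial survey for an optional follow-up survey", and then "Those who do not opt out will be asked to complete a brief (5 minute) follow-up survey 3-6-months post-intervention". Section 5.8 instead has uptake "collected through an opt-out follow-up survey administered 6 months post-intervention". No section links the contact date to the trip month already recorded, and no re-contact is described.

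**Follow-up questionnaire (Appendix 4).** The first question asks whether the planned trip was taken, yes or no. A no leads to how plans changed (cancelled, different destination, "Delayed the trip", other), then to an optional free-text box marked as the end of the survey. A yes skips ahead to the country visited. Between these sits a question on travel to any listed country since November 2024, with its own exit for a no. Next comes a question on visiting a healthcare provider, where a no jumps to mosquito-bite measures. The uptake question comes after all of these.

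**SAP.** Secondary Outcome 3 codes uptake as 1 for yes and 0 for no or not remembered. Section 2.2 says in general terms that missing data will be multiply imputed.

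**The concern.** Uptake is a named secondary outcome and part of the stated hypothesis. A follow-up sent at 3 months complies with Sections 4 and 5.3, yet some participants will not have left. They cannot report pre-travel uptake, and those with the latest departures had the most time to be vaccinated. The observed group would then be smaller and weighted to people with short lead times.

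The routing adds two losses that timing does not cure. Travellers who delayed or went to a different listed country may be sent out unasked, and on-time travellers who saw no provider are not asked at all. The SAP does not say whether people never asked are missing, not applicable or outside the denominator.

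**Working it through.** **1. The plan's own figure.** SAP Section 2.5 gives 175 per group for the primary outcome (effect size 0.30, correlation 0.5, two-sided 0.05, 90% power). With residual SD √(1 − 0.5²) = 0.866, the calculation gives 176 per group; power at 175 is 0.8998. Allowing for 30% non-completion, 350 / 0.70 = 500. The figure reproduces and is not affected here. The documents state no power or sample size for uptake, so 350 completers serves below as the base.

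**2. Routing, traced as printed.**

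| Respondent | Path | Uptake question asked? |
|---|---|---|
| Trip taken, saw a provider | skips to country, provider, uptake | Yes |
| Trip taken, saw no provider | skips to country, provider, mosquito measures | No |
| Trip delayed or to another destination | how plans changed, free text, end | No |
| Trip cancelled | same | No |
| Trip not yet due | no matching response; a no leads to the same exit | No |

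Read literally, nobody reaches the question on travel since November 2024: a yes skips past it and a no ends before it. But that question has its own exit, which has a purpose only if some respondents arrive there. The two instructions conflict. If the free-text ending is ignored, delayed or re-routed travellers who visited a listed country do reach the uptake question. A person still to depart leaves at the second exit, unless some other trip to a listed country had been made. So the not-yet-departed are lost on either reading.

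**3. Share not yet departed at contact.** Let F be the distribution of departure time over 0 to 6 months; the share still to leave at month t is 1 − F(t). The documents give no distribution, so three shapes are assumed: uniform, 1 − t/6; early-weighted Beta(1,2), (1 − t/6)²; late-weighted Beta(2,1), 1 − (t/6)².

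| Contact month | Early-weighted | Uniform | Late-weighted |
|---|---|---|---|
| 3 | 25% | 50% | 75% |
| 4 | 11% | 33% | 56% |
| 5 | 3% | 17% | 31% |
| 6 | 0% | 0% | 0% |

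At month 3 with full response, the uniform shape leaves 350 × 0.50 = 175 completers without an observed value (about 88 to 262 across the other shapes). The zero at month 6 holds only for trips that start as planned.

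**4. What that does to precision (illustration only).** Uptake rates are not in the documents, so pairs are assumed, with full response and equal arms.

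| Assumed uptake | Power, 350 observed | Power, 175 observed |
|---|---|---|
| 10% vs 20% | 0.75 | 0.46 |
| 20% vs 30% | 0.58 | 0.33 |
| 30% vs 45% | 0.83 | 0.54 |

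**The case against.** The strongest reply is that Section 5.8, the data-collection section, already places the survey at 6 months, which lies inside the 3-to-6-month window. If that is the plan, almost nothing is lost to timing and what remains is a wording conflict. This stands as far as it goes, but Sections 4 and 5.3 permit earlier contact, so it cannot be assumed.

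Second, ending the survey for people who did not travel is partly sensible. The SAP outcome is pre-travel uptake, and the question has no clear meaning for a cancelled trip or one to a country without JE risk. This also stands: such respondents should still exit. It does not cover delayed trips or a different listed country.

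Third, the misplaced ending may be a drafting slip. That is plausible, and is why the instructions are described here as conflicting.

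Three stronger readings are tempting and not supported:

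- **That 43% to 57% of uptake data will be lost.** For a November entrant contacted in February, March to May is 3 of 7 listed months (43%), and February to May is 4 of 7 (57%). This assumes everyone is contacted at the earliest permitted time, with trips spread evenly over seven options when eligibility spans six months.
- **That the SAP will impute an outcome that has not yet happened.** Section 2.2 is a general sentence. The defensible statement is that no rule is given for people never asked.
- **That the comparison between arms is biased.** Planned trip month is recorded before randomisation, so timing loss should be similar in both. Exit for changed plans happens after randomisation, so balance there is not guaranteed, but the documents give no sign of a difference.

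**Conclusion.** The point holds on the text. Sections 4 and 5.3 conflict with Section 5.8 on timing, contact is not tied to the trip month, there is no response for a trip still ahead, and the two routing exits contradict each other. The skip for those who saw no provider is explicit.

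The size depends on when contact is made. At 3 months about half of completers would have no observed uptake if departures are uniform, with 25% to 75% under the other assumed shapes. At 6 months the timing loss is near zero for trips that start as planned, and the routing losses remain. Their size cannot be computed, because the documents give no rates for changed plans or provider visits.

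The consequence is reduced precision and an uptake result that describes mainly short-lead travellers. It concerns a secondary outcome from an optional survey and leaves the primary analysis untouched.

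**What to change.** - **Timing.** State one rule in Sections 4, 5.3 and 5.8: contact no earlier than 6 months after entry, or after the stated trip month if that is later. Update the Section 5.12 timeline. With recruitment in month 3, a 6-month contact falls at about month 3 + 6 = 9, beyond the 7 months shown but within the 1-year duration in Section 1.2.
- **Branching.** Add a not-yet-travelled response with re-contact. Send delayed or changed-destination respondents to the question on travel to a listed country, and those who travelled on to the uptake question. Let cancelled trips and trips to non-listed countries exit. Ask the uptake question whether or not a provider was seen.
- **SAP.** Under Secondary Outcome 3, state that people who did not travel to a listed country are outside the pre-travel uptake denominator rather than imputed. Travel is a post-randomisation event, so report by arm how many fall outside and why.
- **If follow-up has already been run.** The current protocol version is dated 17 November 2025, after the last listed trip month. In that case report actual contact dates, uptake by stated trip month, and the numbers never asked.

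The cost is protocol and SAP wording plus a REDCap schedule and branching edit. Uptake data arrive up to 3 months later, with slightly more recall error and attrition.
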